### Safety evaluation

All adverse events will be recorded on the adverse event record sheet by the acupuncturist and participants at any time over the study period. Adverse events include broken needle, unbearable acupuncture pain, local haematoma, infection, dry mouth, constipation and any other discomfort or accident. The intensity and causality of each adverse event will be evaluated and recorded. If any serious adverse events occur as the result of a certain intervention, that intervention will be stopped immediately, and appropriate corrective action will be taken. Any serious adverse events will be reported promptly to the institutional review board within 24 h until 30 days after the end of the trial. If any of the enrolled patients become pregnant, it will also be reported by filling in the “pregnancy notice form” to give to the institutional review board.

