As a main branch of traditional Chinese medicine, acupuncture has been recommended for solving neurogenic bladder dysfunction by the World Health Organization [13]. Our team’s latest OAB system evaluation suggests that electroacupuncture (EA) may reduce urinary frequency, urinary incontinence, and nocturnal urination episodes [14]. However, the evidence does not support the efficacy of EA alone in the treatment of OAB. In the future, high-quality research methods and large sample sizes are needed to confirm the efficacy of EA in OAB. EA is similar to PTNS in some ways; however, the type of EA treatment used in this trial could stimulate not only the tibial nerve (through the acupoint of SP6) but also the 3 sacral (through the acupoint of BL33) and pudendal nerves (through the acupoint of BL35). Integrating PTNS and SNS stimulation points may have good benefits. Some research has been conducted to prove the effectiveness of EA for the treatment of OAB. A study conducted by LU Yujin et al. included 86 OAB patients with EA, and the results showed an overactive bladder symptom score (OABSS) of 8 (CI: 7–9) before treatment and 2 (CI: 4–6) after treatment, with a statistically significant difference (*P* < 0.05) [15]. A randomized controlled trial (RCT) conducted by Wang Yafei et al. suggested that EA had significant clinical efficacy for OAB with a simple operation, and there were no side effects or postoperative complications, which was better than the medicine [16]. Another animal experiment proved that EA could effectively inhibit bladder overactivity, and the effect had acupoint specificity [17].

Thus, based on the aforementioned historical study and clinical experience, our team designed this prospective, multi-centre, RCT study protocol with a large sample size to evaluate the effectiveness and safety of EA compared with solifenacin for OAB.

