### Procedure

After randomization, therapeutic assessment will be conducted at six time points: baseline and at the end of weeks 4, 8, 12, 20, and 32. Full-time evaluators will be responsible for filling out, issuing, recovering and recording the urination diary card and case report form (CRF) during the trial.

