### Electroacupuncture (EA)

According to traditional Chinese medicine theory, the results of previous studies and the opinions of acupuncture experts at Guang’anmen Hospital, China Academy of Chinese Medical Sciences, the following main acupoints will be selected: BL23 (Shen Shu), BL33 (Zhong Liao), BL35 (Hui Yang), and SP6 (San YinJiao). All acupoints are bilateral. The locations of each acupoint conform to the standard defined by the World Health Organization [21].

After sterilizing the acupoint areas, for BL33, a needle will be inserted at a point 1 cm upwards and outwards from the 3rd posterior sacral foramina into the 3rd posterior sacral foramina in a slant and in an inward and a downward direction as well as at an angle of approximately 45–70 degrees to the midline using a 0.30 mm × 75 mm needle inserted approximately 60–70 mm deep. For BL35, a needle will be inserted (needle size 0.30 mm × 75 mm) approximately 60–70 mm deep at a slant in an outward and upward direction. For BL23 and SP6, needles will be directly inserted approximately 25–30 mm deep with 0.30 mm × 40 mm needles. The duration of reinforcing- reducing manipulation of twirling and rotating needle should be used for 1 min to achieve de qi (a composite of sensations including acid, hemp, bilge sensation, warm and pulse, these feelings may even travel along the meridians), which is recognised to be an essential component for acupuncture efficacy. Then electrodes from the EA apparatus will be attached transversely to the needle handles for bilateral BL33 and BL35 with a current intensity of 2 to 6 mA and with a current intensity of 1 to 2 mA for ipsilateral BL23 and SP6. All current intensities will be as high as can be tolerated. The current frequency will be a continuous wave of 10 Hz, and the stimulation will last for 30 min. First, EA will be applied for three sessions per week for a total of 4 weeks, followed by twice a week for 8 weeks a total of 28 sessions over a course of 12 weeks.

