### Sham electroacupuncture (SA)

The non-acupoints will be located 2 cm outward for BL33, BL35, BL23 and SP6. After local skin disinfection, a 0.2 mm × 25 mm needle will be used for insertion at a depth of approximately 2–3 mm until the needle can stand erectly. The manipulation of the needle to de qi will not execute, and the current intensity will be 0.1–0.3 mA (slight electrical stimulation is perceived by the patient). The connection method for the electrode and the number of sessions of acupuncture will be the same as those for the EA group.

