### Solifenacin

Solifenacin will be taken orally at a dose of 5 mg once daily for 32 weeks. It will be suggested that patients who can tolerate the drug should continue to take the drug; the drug should be withdrawn in cases of failure; and patients with severe adverse reactions should stop taking the medicine at any time, which will be recorded.

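### The adverse-event recording rule gives unequal ascertainment between the acupuncture arms and solifenacin, so crude EA–solifenacin safety rates would mix ascertainment with exposure

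*Protocol article*

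**What the plan says.** The Background of the protocol article gives the trial's purpose as "to evaluate the effectiveness and safety of EA compared with solifenacin for OAB", so safety against the drug is a stated aim.

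The Safety evaluation section fixes who records events and when: "All adverse events will be recorded on the adverse event record sheet by the acupuncturist and participants at any time over the study period". Its list of event types covers needling events, dry mouth, constipation and any other discomfort, so drug-type events are expected.

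Contact and exposure by arm:

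- **EA (a 12-week course):** "three sessions per week for a total of 4 weeks, followed by twice a week for 8 weeks a total of 28 sessions".
- **SA:** as many sessions as EA, according to the sham section.
- **Drug arm:** "Solifenacin will be taken orally at a dose of 5 mg once daily for 32 weeks". The same section provides for earlier stopping, for lack of effect or for a severe reaction.
- **Every arm:** Procedure schedules assessments at baseline and weeks 4, 8, 12, 20 and 32.

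Procedure also gives dedicated evaluators charge of the diary cards and the CRF. The Safety evaluation section does not mention these evaluators.

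**The concern.** The one staff member named as a recorder is someone a solifenacin patient has no treatment reason to meet. In the acupuncture arms that person gives the treatment under test, knows the allocation (the Discussion accepts that acupuncturists cannot be blinded) and is present several times a week for 12 weeks. In the drug arm the stated rule leaves recording to the participant, whenever the participant chooses. The article describes no enquiry put to all arms in the same way at the same times.

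More opportunity to report usually means more events recorded. Against that, the drug arm has a longer planned time on treatment in which events can occur. If events are simply counted over the whole study, a difference between EA and solifenacin could reflect who was asked, how often, or how long treatment lasted, rather than the treatments themselves. This matters because the Background gives drug adverse effects as a problem with current treatment, and the Discussion presents few adverse effects as an advantage of acupuncture.

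**Working it through.** **Step 1: the plan's own figure.** Sessions = 3 per week × 4 weeks + 2 per week × 8 weeks = 12 + 16 = 28. This reproduces the 28 in the Electroacupuncture section, and the sham section gives SA the same number.

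**Step 2: described contacts.** The assessments after baseline are at weeks 4, 8, 12, 20 and 32: three by week 12, five in all.

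| Period | EA or SA | Solifenacin |
|---|---|---|
| To week 12 | 28 (every assessment on a session day) to 28 + 3 = 31 (none) | 3 |
| To week 32 | 28 + 2 = 30 to 28 + 5 = 33 | 5 |

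The solifenacin counts are floors, because visits to supply the drug are not described.

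**Step 3: exposure.** Planned time on treatment is 32 weeks against 12, and 32/12 = 2.67. The 32 weeks is a maximum, since earlier stopping is allowed. The calendar window of observation is the same in all arms.

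**Step 4: what exposure alone could do (assumed).** The documents give no event rates. Assume the same constant hazard on either treatment, no events off treatment and full persistence on the drug. With p12 the 12-week risk, p32 = 1 − (1 − p12)^(32/12).

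| Assumed p12 | p32 | Ratio p32/p12 |
|---|---|---|
| 5% | 12.8% | 2.56 |
| 10% | 24.5% | 2.45 |
| 20% | 44.8% | 2.24 |
| 30% | 61.4% | 2.05 |

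**Step 5: what ascertainment alone could do (assumed).** Let a fraction c of events be captured on solifenacin and all events be captured on EA. With equal true risk, the solifenacin-to-EA ratio for weeks 0–12 equals c: 0.5 to 0.9 for c from 50% to 90%.

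**Step 6: both together.** The whole-study ratio is c × p32/p12.

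| Assumed p12 | c = 0.5 | c = 0.75 | c = 0.9 |
|---|---|---|---|
| 10% | 1.22 | 1.84 | 2.20 |
| 20% | 1.12 | 1.68 | 2.02 |
| 30% | 1.02 | 1.53 | 1.84 |

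If drug events all came early, with none after week 12, then p32 = p12 and the whole-study ratio falls back to c, that is 0.5 to 0.9. Two treatments that are equally hazardous during use could therefore show a ratio below or above 1. At p12 = 20% the span is 0.5 (c = 0.5, no events after week 12) to 2.24 (full capture, constant hazard).

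**Step 7: EA against SA.** Sessions, recorder and treatment period are the same, so neither mechanism separates these two arms.

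**The case against.** The strongest reply is that the drug arm is not unobserved. Participants record events in every arm, at any time, so recording does not depend on visits. The record sheet covers drug-type events. Stopping the drug for a severe reaction is recorded, a urologist at each centre assesses severe side effects (Withdrawal criteria), and evaluators handle the CRF in all arms. The article is a condensed account, and the full protocol may name someone for the drug arm. No between-arm test of adverse events and no cumulative rate is stated. Reporting windows and exposure adjustment are usual content of an analysis plan, which is not shown, and different durations belong to the treatment strategies being compared.

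Most of this stands, and it limits the point. A reader might infer that nobody records events on solifenacin. The documents do not say that; they show only that no staff recorder is named for that arm. A reader might also infer that longer exposure must make the drug look worse. That does not follow either: weaker capture works the other way, 32 weeks is a maximum, and the constant hazard is an assumption.

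What does not fall away is the recording rule itself. It is stated, not left out, and it adds a treating clinician's record in two arms only. A week 0–12 or per-patient-time analysis can deal with exposure, but no later analysis recovers events that were never elicited. The urologist's role appears as a withdrawal criterion, not as routine recording.

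A further fair objection concerns the remedy. If the blinded evaluators asked about dry mouth or needle pain at weeks 4 and 8, they could learn the allocation before the primary OABSS assessment at week 12. That is right, and the change proposed below avoids it.

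**Conclusion.** The point holds for EA, and equally SA, against solifenacin. Applied as written, the rule gives the acupuncture arms participant recording plus an unblinded treating clinician at up to 28 sessions by week 12. The solifenacin arm gets participant recording, no named staff recorder and three described assessments in the same period. Planned exposure differs by up to 2.67-fold. Crude whole-study rates would mix the two effects, and their net direction cannot be determined from the documents.

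The contact counts and the exposure ratio come from the article. The ratios of 0.5 to 2.24 are illustrations that rest on assumed risks, assumed capture fractions and two assumed hazard patterns; they do not predict this trial's results.

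It would be tempting to conclude that safety rates cannot be compared between any of the arms. The documents do not support that, because EA and SA are balanced on sessions, recorder and duration. The primary efficacy comparison is not touched. This is a weakness in safety data collection that should be corrected, not a fatal fault.

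**What to change.** Change the Safety evaluation section so that participants in all three arms complete the same fixed adverse-event checklist at the assessments already scheduled for weeks 4, 8, 12, 20 and 32. Collect it after the OABSS and keep it from the blinded outcome assessor at every visit. It could, for example, be sealed and handed to the research assistants who, under Randomization and blinding, take no part in treatment or evaluation.

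Define the EA–solifenacin safety comparison as checklist events in weeks 0–12, when both treatments are planned to be in use and every arm is asked the same questions equally often. Keep recording by acupuncturists and at any time by participants, but report acupuncturist-recorded events separately, and report weeks 12–32 separately.

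The cost is a few minutes per visit and some care in handling the sheets; no extra staff are needed. No dose, treatment duration or clinical rule changes. The Trial status section reports 23 participants recruited of the planned 420, so at that point a change would have covered nearly all of the sample.

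### The adverse-event list attaches an intensity qualifier to acupuncture pain but none to dry mouth or constipation, so bearable needling or current pain may go unrecorded and tilt the descriptive safety comparison towards electroacupuncture

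*Protocol article*

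**What the plan says.** The Safety evaluation section of the protocol article gives one description of what counts: "Adverse events include broken needle, unbearable acupuncture pain, local haematoma, infection, dry mouth, constipation and any other discomfort or accident". It says who records events: "All adverse events will be recorded on the adverse event record sheet by the acupuncturist and participants at any time over the study period". It then adds: "The intensity and causality of each adverse event will be evaluated and recorded".

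Three other parts of the article bear on this sentence.

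- **Electroacupuncture (EA).** On current, within stated bounds of 2 to 6 mA for BL33 and BL35 and 1 to 2 mA for BL23 and SP6: "All current intensities will be as high as can be tolerated". The section also has the practitioner elicit de qi, described as "a composite of sensations including acid, hemp, bilge sensation, warm and pulse" and as something "which is recognised to be an essential component for acupuncture efficacy".
- **Sham electroacupuncture (SA).** De qi is not sought: "The manipulation of the needle to de qi will not execute".
- **Background.** Dry mouth and constipation are named among the effects of antimuscarinic agents. The section closes by giving the trial's purpose as "to evaluate the effectiveness and safety of EA compared with solifenacin for OAB".

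**The concern.** A safety comparison between a needling procedure and a drug is fair only if events enter the count at the same threshold in each arm. Here the listed term for pain from acupuncture requires it to be unbearable, while the two listed drug effects qualify at any intensity. A participant or acupuncturist who takes the qualifier at its word would leave bearable pain off the sheet, and mild dry mouth in the solifenacin arm would still go on it.

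The comparative safety statement is at stake. Safety of EA against solifenacin is an aim of the trial, and the Background and Discussion argue for acupuncture partly on the ground of few adverse effects. If the recording rule trims the lower end of one arm's events, part of any observed advantage could come from the rule.

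**Working it through.** No stated figure is in dispute, since the article gives no adverse-event rate and no power for safety. The check is a comparison of passages, followed by a test of whether any size can be attached.

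**Step 1: the list, item by item** (arm attribution is mine, from the nature of each event and the Background).

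| Listed event | Arm in which it is expected | Intensity qualifier |
|---|---|---|
| Broken needle | EA, SA | none |
| Acupuncture pain | EA, SA | unbearable |
| Local haematoma | EA, SA | none |
| Infection | not tied to one arm | none |
| Dry mouth | solifenacin | none |
| Constipation | solifenacin | none |
| Catch-all (other discomfort or accident) | all | none |

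Pain is the single item with a threshold.

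**Step 2: two readings of the sentence.**

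- *Narrow.* The qualifier has meaning, so bearable acupuncture pain is not an event.
- *Broad.* The catch-all takes in bearable pain, so it is an event and the qualifier is redundant.

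The sentence supports both, and no other section chooses between them.

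**Step 3: is bearable pain foreseeable?** The EA section sets current at the highest level the participant tolerates, within the stated bounds. Discomfort that is felt but tolerated is therefore to be expected in at least some participants, and the two readings treat exactly this group differently.

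**Step 4: can it be recovered later?** Intensity and causality are evaluated for each adverse event, that is, after something has been counted as one. An analysis plan can select among recorded events. It cannot restore events that were never written down.

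**Step 5: direction.** Consider pain alone. Let *u* be the percentage of EA participants with unbearable pain, *a* the percentage with pain of any intensity, and *s* the percentage on solifenacin with dry mouth or constipation. The recorded difference is *u* − *s* on the narrow reading and *a* − *s* on the broad one. Since *a* ≥ *u*, the narrow reading can only move the difference in EA's favour, by *a* − *u*.

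**Step 6: size.** Every rate here is an assumption: *a* from 5% to 30%, *u* from 0% to 3%, *s* from 10% to 20%.

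- Narrow: from 0 − 20 = −20 to 3 − 10 = −7 points; at the midpoints, 1.5 − 15 = −13.5.
- Broad: from 5 − 20 = −15 to 30 − 10 = +20 points; at the midpoints, 17.5 − 15 = +2.5.
- Shift *a* − *u*: from 5 − 3 = 2 to 30 − 0 = 30 points; at the midpoints, 17.5 − 1.5 = 16.

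The shift runs from negligible to large, depending wholly on assumed inputs. The direction follows from the text; the size does not.

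**The case against.** The strongest reply is that the list is open. It is introduced as a set of inclusions and ends with a catch-all, and both Outcome measures and Safety evaluation say that all adverse events will be recorded. Bearable pain then falls under the catch-all without strain. This stands to the extent that the article cannot be said to exclude bearable pain. It does not remove the conflict, because on that reading the qualifier has no function, and those filling in the sheet have to guess that it should be ignored.

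Other points also carry weight:

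- **The list is not tilted throughout.** Broken needle and local haematoma are acupuncture harms and carry no threshold. The point concerns pain alone.
- **Intensity is recorded in every arm.** This allows comparison at equal grade, but only among events that reach the sheet.
- **Current is capped.** For some participants the upper bound may be reached before the limit of tolerance, so the text does not place EA discomfort just short of unbearable in everyone.
- **Training and the sheet's instructions may settle the matter.** The article mentions training of all researchers but states no rule on this point. Such detail may sit in the full protocol. The objection here is to wording the article does fix.
- **EA acceptance is scored at week 12 on a 5-point scale.** This measures how acceptable EA was and does not replace a record of events.

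Two stronger readings are tempting and not supported. A reader might infer that the catch-all makes de qi an adverse event in nearly every EA participant. The article calls de qi a set of sensations and treats it as part of how the treatment works. It never calls it discomfort, so this needs a strained literal reading. A reader might also infer that the safety comparison would change sign if all pain were counted. That depends on assumed rates: with any-intensity pain at 5% and solifenacin events at 10% to 20%, EA stays lower (5 − 10 = −5 to 5 − 20 = −15 points).

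**Conclusion.** The point holds as a minor one. The adverse-event sentence conflicts with itself on whether bearable acupuncture pain counts, and one of its two natural readings sets a higher bar for that pain than for the listed drug effects. If sites follow that reading, the descriptive EA-versus-solifenacin comparison is tilted towards EA, and the loss cannot be repaired in analysis.

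The direction rests on two premises: that some EA participants have pain they can bear, which the tolerance-guided current makes likely, and that some recorders take the qualifier literally, which the wording permits but does not require. No size can be stated. The article describes no formal safety test, and the primary outcome is the change in overactive bladder symptom score, so the non-inferiority conclusion is untouched.

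**What to change.** Three changes, none of which alters treatment:

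1. In Safety evaluation, and on the adverse-event record sheet, replace the listed pain item with needling or current pain of any intensity.
2. State explicitly whether the intended de qi sensation during a session counts as an adverse event. The sponsor can decide either way, provided the same rule applies at every hospital.
3. Use the intensity already recorded for each event to report the between-arm comparison twice: for any event, and at the same intensity grade in all three arms.

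The cost is a wording change on a form and a line in site training. The downside is a higher recorded EA event rate, mostly of mild events, which the same-grade comparison puts in proportion. At the status given in the article, 23 of 420 participants had been recruited (23/420 = 5.5%), so a change made then would have covered the whole course of the remaining 397. For anyone already treated, bearable pain that was not written down cannot be reconstructed, and the report should say under which wording their events were collected.

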### Quality control

A central randomization system will be adopted, which will be undertaken by the China Academy of Chinese Medicine Sciences to reduce selection bias. Before starting the trial, all researchers from the 4 trial centres will undergo training. All collected data will be timely input into the ClinResearch Electronic Data Capture System developed by the Clinical Evaluation Center of the China academy of Chinese Medical Sciences. A 3-level monitoring system will be established to periodically check the performance of the trial. The outcome assessments and the completion of CRF and data management will be closely supervised.

